| 3. Pubertal progress | Pubertal staging (Tanner staging) is conducted by physical examination or by self-report, and reports the degree to which young people have progressed from prepubertal (stage 1) to fully puberty (stage 5) in 3 areas for each birth registered sex.  a. genital and pubic hair stage and testicular volume in males;  b. Breast and pubic hair stage and menarcheal status in females.  For analysis the three values for each birth registered sex were combined into an overall stage i.e. 2 through 5. This is common practice in clinical research. | Baseline and end of follow-up | The aim of GnRHa treatment is to prevent further progression in puberty during treatment. Young people will be categorised as stage 2 through 5 at baseline and monitored for pubertal progression.  Hypothesis: No pubertal progression | Baseline: proportions in each Tanner stage  Follow-up: proportions with any pubertal progression or not |
| B. MEDICAL SAFETY | |  |  |  |
| 1. Safety bloods | 1. Liver & renal function  2. Full blood count  3. Bone profile  4. Basal endocrinology  5. Vitamin D | 12-monthly.  Liver and renal function also assessed at 3m. | Safety bloods were designed to assess impact on liver and renal function, basal endocrinology and basic haematology.  Hypotheses: No change in any measured parameters | Individual tests are not outcomes of interest aside from overall safety. Bloods were taken at regular intervals but for parsimony will reported at 12, 24 and 36 months. Reporting of outcomes will be categorical in terms of normality of each test, with numbers with identified abnormalities of any test. The reference norms for the laboratory where testing was done (UCLH) will be used to define normality. No statistical testing will be done. |
| 2. Adverse events | Patient report of adverse events from   1. clinic visits 2. patient interviews   At each clinic visit, patients were routinely asked about adverse events. | At 6, 12, 24, 36 and 48m | Expected adverse effects were not specified in the Protocol. Any adverse events noted at clinic visits will be reported.  Note that formal semi-structured interviews at 6-12 months after commencement also sought information on side-effects and these data will be contribute to side-effect reporting. | Presence or absence of reported side-effects |
| C. BONE HEALTH |  |  |  |  |

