### Analysis methods

The original protocol stated: “All the data will be recorded and the questionnaires scored. Descriptive statistics including means and standard deviations will be reported as well as parametric and non-parametric tests as appropriate.”

Due to the small sample size, analyses will be largely restricted to descriptive statistics and elementary statistical tests.

Outcomes will be reported at baseline and 12, 24 and 36 months. Outcomes at 48 months will not be reported due to very low numbers.

For categorical outcomes, simple descriptive statistics will be reported.

For continuous measures we will formally test change using paired t-tests for the significance of the before/after difference of the main scales as specified above. For other scales and subscales we will calculate means and 95% CI at baseline and follow-up, showing baseline mean for both the whole sample and for the sample with data at the follow-up point.

Predictors of outcome: There are multiple hypotheses that could be made about whether individual demographic, physical or psychological factors relate to differences in outcomes, either by confounding or potentially more causally. Our design and study size mean that exploration of such hypotheses is not possible without high risk of chance findings. We will restrict analysis of predictors of outcome to two factors, birth registered sex and pubertal stage at baseline. We will restrict analysis to three continuous outcomes measured at baseline and 12 months. These outcomes were chosen as key outcomes across physical and mental health:

1. bone mineral density (BMD) in the lumbar spine
2. YSR total t-score
3. CGAS score

We will do this by linear regression of follow-up score on baseline score, adding each predictor separately to each model and considering the interaction of predictor with baseline score. If both factors appear to predict outcome, we will include these in a multivariable model and use backwards stepwise selection to identify the best predictive model.

We note that the nature of the patient group and their data are both unusual and highly sensitive, so that publication of findings may potentially identify individuals, particularly given the small sample size. We will consult with data protection experts to ensure that personal data are not disclosed.

Dissemination and Outputs

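### Pubertal progression has no at-risk denominator: participants already at overall Tanner stage 5 at baseline would, on the plain reading, count as not having progressed

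*SAP*

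**What the plan says.** Everything that bears on this is in the SAP, mostly in the Outcomes table, row A.3 (Pubertal progress).

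- **Scale.** Tanner staging runs from stage 1 (prepubertal) to stage 5 (full puberty). Three areas are recorded for each birth-registered sex.
- **Analysis variable.** "For analysis the three values for each birth registered sex were combined into an overall stage i.e. 2 through 5". The rule for combining the three values is not given.
- **Who is followed.** "Young people will be categorised as stage 2 through 5 at baseline and monitored for pubertal progression".
- **Hypothesis.** "Hypothesis: No pubertal progression".
- **Summaries.** At baseline: "Baseline: proportions in each Tanner stage". At follow-up: "Follow-up: proportions with any pubertal progression or not".

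The Analysis methods section adds one general rule: "For categorical outcomes, simple descriptive statistics will be reported". It also plans to use baseline pubertal stage as a predictor, but only for lumbar spine BMD, the YSR total t-score and the CGAS score.

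**The concern.** The follow-up summary is binary: progressed, or not. For someone at overall stage 5 at baseline only one answer is possible. The text foresees such participants, places them in the monitored group and gives no instruction to set them aside.

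The row states that treatment aims to prevent further pubertal progression, so this proportion speaks directly to whether that aim was met. Including people who are not at risk moves it in one direction only, towards the stated hypothesis. A reader would then take part of the no-progression figure as an effect of treatment when it reflects where participants started.

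**Working it through.** The SAP states no target, rate or sample size for this outcome, so there is no figure to reproduce. The check is the arithmetic of the denominator.

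**Inputs**

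- Possible overall stages at baseline: 2 to 5 (Outcomes table, A.3).
- Highest stage: 5 (same row).
- p, the progression rate among those at stages 2–4 at baseline: not in the SAP; 30% assumed.
- f, the share at stage 5 at baseline among those with a follow-up stage: not in the SAP; 0%, 10% and 30% shown.

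**Step 1: reported progression.** Those at stage 5 add nothing to the numerator but stay in the denominator:

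reported = p × (1 − f) + 0 × f = p × (1 − f)

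| f | Calculation | Reported progression | Rate among those at risk |
|---|---|---|---|
| 0% | 0.30 × 1.00 | 30% | 30% |
| 10% | 0.30 × 0.90 | 27% | 30% |
| 30% | 0.30 × 0.70 | 21% | 30% |

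**Step 2: floor on the no-progression figure.** Reported no progression = 1 − p × (1 − f). If everyone at risk progressed (p = 1), this equals f. The figure can never fall below the stage 5 share: at f = 10% it stays at 10% or more even if treatment prevents nothing.

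**Step 3: can a reader undo it?** The baseline stage distribution will be reported, so the obvious repair is to divide by (1 − f). That works only if the baseline f matches the f among those with a follow-up stage. As an illustration, suppose stage 5 makes up 30% of the baseline sample but 10% of those followed, and 27% is reported. Dividing by the baseline value gives 0.27 / 0.70 = 38.6%; the rate among those at risk is 0.27 / 0.90 = 30%. The published baseline table therefore allows an approximate correction only.

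**Step 4: does another section set the denominator?** No. The general rule for categorical outcomes asks for simple description and is silent on who is counted. The analysis by baseline pubertal stage covers three other outcomes.

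**The case against.** The case on the other side has real force, and it limits the point in several ways.

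- **The SAP does not say that everyone is in the denominator.** A reader might infer that it fixes a wrong denominator. It names none, and leaving out those at stage 5 would not contradict its wording. This stands. Inclusion is the plain reading because stages 2 to 5 are categorised and followed with no exclusion, but it is an inference.
- **The hypothesis is not true by construction.** A reader might infer that it is, at least in part. But the hypothesis is that there is no progression, so a single progressor contradicts it whatever the denominator. Those at stage 5 hide no progressor; the count is unchanged and only the percentage is diluted.
- **The number at stage 5 may be small or zero.** Listing stage 5 as a category does not show that anyone was in it. The SAP supports no claim that the share is large.
- **This is not the only evidence of suppression.** Rows A.1 and A.2 of the Outcomes table plan hormone suppression at 6 to 12 months, hormone means with 95% CI, and height z-scores. None of these has the Tanner ceiling.
- **No test is affected.** The outcome is descriptive, with no p-value or success threshold.
- **A component might still change.** The combining rule is not given, and if any progression were meant to include single components, someone at overall stage 5 might register a change. That is possible, but the row names the combined stage as the variable for analysis, and that stage cannot rise above 5.

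What remains is that a descriptive proportion still needs a denominator of people to whom the event can happen, and publishing the baseline distribution repairs this only approximately.

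**Conclusion.** The point holds as a modest one. Followed as written, the plan would produce a progression percentage diluted by the factor (1 − f), always in the direction of the hypothesis. With p = 30%, the reported figure falls by 3 percentage points at f = 10% and by 9 at f = 30%; at f = 0 nothing changes. Both p and f are assumptions, because the SAP gives neither.

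The conclusion rests on two readings: that participants at stage 5 are counted, since no exclusion is stated, and that progression means a rise in the overall stage. It should not be taken as showing that the hypothesis cannot fail, that suppression as a whole is misjudged, or that any formal test is wrong. The change is still worth making, because the bias runs one way and is removed at almost no cost.

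**What to change.** Replace the follow-up entry in the Outcomes table, row A.3, with:

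> Follow-up: number and proportion with any increase in overall stage among participants at stage 2–4 at baseline with a follow-up stage; the number at stage 5 at baseline is shown separately as not at risk.

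This also settles that progression is judged on the combined stage. A breakdown by baseline stage or by birth-registered sex is optional. It is not needed to cure the problem, and small cells would have to go through the consultation with data protection experts planned under Analysis methods; the SAP contains no small-cell rule of its own.

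The cost is one sentence and no new data. The downside is a smaller denominator, hence a less precise proportion, and possibly a less favourable figure.

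### Liver and renal tests at 3 months are collected but not reported, and the SAP contradicts itself on whether 48-month adverse events are reported

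*SAP*

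**What the plan says.** In the SAP's Outcomes table, section B (Medical safety), row 1 sets a 12-monthly schedule for safety bloods and adds: "Liver and renal function also assessed at 3m". The same row then restricts what is shown: "Bloods were taken at regular intervals but for parsimony will reported at 12, 24 and 36 months". The form of reporting is "Reporting of outcomes will be categorical in terms of normality of each test, with numbers with identified abnormalities of any test", without statistical testing.

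Row 2 of section B covers adverse events. Its timing entry is "At 6, 12, 24, 36 and 48m", and its reporting promise has no visit limit: "Any adverse events noted at clinic visits will be reported".

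Analysis methods sets a general rule for all outcomes: "Outcomes will be reported at baseline and 12, 24 and 36 months". It continues: "Outcomes at 48 months will not be reported due to very low numbers". Neither sentence makes an exception for the safety domain.

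**The concern.** The 3-month test is the first scheduled look at liver and renal function on treatment. A reporting rule that begins at 12 months hides two kinds of finding: an abnormality at 3 months that was normal again by 12 months, and an abnormality in a participant who had no test at 12 months or later. Brevity is a weak reason to leave these out, because the row plans only counts of normal and abnormal results. One more count raises no multiplicity or precision problem.

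On adverse events, an analyst following the outcome row would report 48-month events, and one following Analysis methods would not. Small numbers are a good reason not to present means and confidence intervals. They are not a reason to withhold a count of events with its denominator.

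At stake is whether the published safety account covers everything that was collected.

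**Working it through.** The SAP gives no figure to reproduce here. The check compares the visits at which safety data are collected with those at which they are reported.

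| Safety outcome | Collected (Outcomes table) | Reported under its own row | Reported under Analysis methods |
| --- | --- | --- | --- |
| Liver and renal function | 3 months, then 12-monthly | 12, 24, 36 months | Baseline, 12, 24, 36 months |
| Other safety bloods | 12-monthly | 12, 24, 36 months | Baseline, 12, 24, 36 months |
| Adverse events | 6, 12, 24, 36, 48 months | Any noted at a clinic visit | Visit list of 12, 24, 36 months after baseline; 48 months excluded |

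**Liver and renal function at 3 months.** Scheduled post-baseline time points up to 36 months are 3, 12, 24 and 36, which is 4. Reported time points are 12, 24 and 36, which is 3. Unreported: (4 − 3)/4 = 1/4 = 25% of time points, and it is the earliest one. The row and the general rule agree in leaving it out, so this is an omission and not an ambiguity. It affects one of the five blood-test groups in the row; the other four have no listed 3-month test.

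**Direction of the effect.** Let A be the participants with an abnormal liver or renal result at 3 months, and B those with an abnormal one at 12, 24 or 36 months. The number abnormal at any of the four visits is |A ∪ B| = |B| + |A not in B|. The planned visits can show at most |B|. The shortfall, |A not in B|, lies between 0 and |A|. It is 0 if every 3-month abnormality was also found later, and |A| if none was. It cannot be negative, so the omission can only lower the number of people reported as ever abnormal. The SAP gives neither |A| nor |B|, so the shortfall cannot be sized.

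**Adverse events.** Five visits are listed. Under the outcome row, events from 5 of 5 are reported. Under Analysis methods read literally, 3 of 5 fall on the visit list; 6 months is not on it, and 48 months is expressly excluded. The two instructions cannot both be followed for 48-month events.

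**Bloods at 48 months.** A 12-monthly schedule implies such tests for anyone followed that long, but the row names no 48-month visit. If any were taken, both the row and the general rule leave them out.

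**The case against.** The strongest reply is that the specific outcome rows must govern over the general visit list. Read literally, that list would also remove the hormone-suppression report at 6 to 12 months, the 6-month satisfaction assessment and the decision at the end of the treatment pathway, all of which their rows plainly intend to report. On that reading, the adverse-events row keeps everything noted in clinic. This is persuasive for 6-month events. It does not settle 48 months, because the exclusion there is a separate, explicit sentence with no exception.

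The 3-month omission is also openly declared with its reason, and an abnormality persisting to a reported visit would still be counted. Both points are fair. They narrow what can be lost to transient abnormalities and to people with no later test, but they do not restore those results.

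A reader might infer more than the SAP supports:

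- *That 48-month adverse events are removed by rule.* They are not, since the outcome row promises to report them. The text is contradictory, which leaves the matter open.
- *That the plan is shown to bias its safety conclusion.* The absence of change in the bloods row is a hypothesis, and only counts are planned. No 3-month abnormality and no early stopper is documented. The end-of-pathway decision is described as following at least 12 months of treatment, and the wish to continue is recorded at each clinic visit, so early stopping would not be invisible.
- *That there is no baseline comparator.* Medical safety is among the domains assessed at baseline, and Analysis methods includes baseline in the reported visits. What separate visit totals cannot show is whether a given person's abnormality is new; a within-person count would be a refinement.

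Disclosure is a genuine constraint with very small cells, but the SAP already plans to consult data-protection experts on it.

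**Conclusion.** The point holds in two parts. First, the SAP collects liver and renal results at 3 months and leaves them out of its reporting; this is 1 of 4 scheduled time points up to 36 months, for one of five blood-test groups. The direction is known, because the number ever reported as abnormal can only fall, but the amount is not and may be zero. Second, the adverse-events row and the 48-month exclusion in Analysis methods contradict each other and must be reconciled.

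This rests on reading the reporting visits in the bloods row as complete and the 48-month sentence as covering safety outcomes, since no exception is stated. The SAP gives no numbers for early stopping or 48-month follow-up, so no effect in participants or events can be calculated. The point is a worthwhile correction to safety reporting. It is not evidence that the trial's safety findings are wrong.

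**What to change.** In the safety-bloods row, keep the planned tables at 12, 24 and 36 months and add two items:

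1. the number of participants with an abnormal liver or renal result at 3 months, with the number tested as denominator;
2. for each test, the cumulative number of participants with any abnormal post-baseline result, split by whether that test was normal at baseline.

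In Analysis methods, state that the visit restriction and the 48-month exclusion do not apply to adverse events, or to any safety bloods taken at 48 months, and that these are reported as counts over all follow-up, subject to the data-protection consultation already planned.

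No new data are needed. The cost is one extra small table, one clarifying sentence and some handling of small cells to avoid disclosure.

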### Outcomes

Outcomes at baseline and follow-up were assessed in four domains:

1. Puberty and growth
2. Medical safety
3. Bone health
4. Psychological function

Two outcomes were assessed only during or after treatment.

1. Treatment satisfaction
2. Decision made at the end of treatment.

The Table below lists the specific outcomes from each domain, along with their expected or hypothesised change from baseline and the analytic plan for each outcome.

| **Outcome** | **Description and measurement** | **Timing** | **Expected or hypothesised change on GnRHa** | **How assessed for study outcomes** |
| --- | --- | --- | --- | --- |
| A. PUBERTY & GROWTH | |  |  |  |
| 1. Gonadotropins and sex steroids | Gonadotropins (LH, FSH; in both sexes), testosterone (in birth-registered males) and oestrogen (birth-registered females) | At 6 and 12 months then annually | The aim of GnRHa treatment was to suppress LH and FSH production, leading to the ‘turning off’ of gonads and therefore suppression of testosterone or oestrogen (depending on birth registered sex).  Hypothesis: that hormones will be suppressed to prepubertal levels by 6 to 12 months. | a. Categorical: Report of whether sex steroids and gonadotropins were suppressed at 6 to 12 months  b. Mean value and 95% CI for hormones at 12, 24 and 36 months |
| 2. Growth | Height, weight and calculated BMI | 6 monthly initially and thereafter 12-monthly | Height: Height growth during puberty is dependent on the twin effects of sex steroids (oestrogen or testosterone) and growth hormone. The pubertal growth spurt occurs around Tanner stage 2-3 in females and stage 3-4 in males. GnRHa treatment is expected to dramatically reduce height growth compared to adolescent peers who are growing rapidly. This will show as only small growth in height but a fall in height z-score (i.e. standard deviation score adjusted for age and sex).  Hypothesis: height velocity will be reduced to prepubertal levels, with a matching fall in height z-score.  Weight and BMI: No definitive hypotheses. We will examine weight and BMI standardized for age and sex through use of weight and BMI z-score. | z-scores for height, weight and BMI calculated for age and sex at 12, 24 and 36 months using the UK 1990 growth reference.  Analysis will be restricted to calculation of means and 95% confidence intervals (95% CI) at each time point, and no statistical testing will be done |

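### The safety-bloods summary reports normal or abnormal status at each visit and cannot separate abnormalities present before treatment from new ones, although its hypothesis is one of no change

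*SAP*

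**What the plan says.** The entry is in the SAP, Outcomes table, B. Medical safety, 1. Safety bloods. It covers liver and renal function, full blood count, bone profile, basal endocrinology and vitamin D.

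- Hypothesis: "Hypotheses: No change in any measured parameters".
- Form of report: "Reporting of outcomes will be categorical in terms of normality of each test, with numbers with identified abnormalities of any test".
- Times: "Bloods were taken at regular intervals but for parsimony will reported at 12, 24 and 36 months". Baseline is not named in the row.
- Definition of abnormal: "The reference norms for the laboratory where testing was done (UCLH) will be used to define normality". The coverage of those ranges is not given.
- Status: "Individual tests are not outcomes of interest aside from overall safety", and "No statistical testing will be done".

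Two general statements bear on the row. The opening of Outcomes says "Outcomes at baseline and follow-up were assessed in four domains", and medical safety is one of the four. Analysis methods says "Outcomes will be reported at baseline and 12, 24 and 36 months". Categorical outcomes are to receive simple descriptive statistics. No shift table, definition of a new abnormality or within-person change is given for bloods anywhere in the SAP.

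**The concern.** The hypothesis is about change and the summary is about status. A participant whose result was out of range before treatment counts the same at 12 months as one whose result became so on treatment. Equal counts at two visits could hide some participants returning to normal while others became abnormal. Movement inside the reference range does not appear at all.

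This matters because the row is the SAP's plan for reporting the safety blood tests. A high count could be read as harm when much of it was there at the start. A stable count could be read as reassurance when its members had changed.

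The SAP handles the point better elsewhere. Pubertal progress is classified by progression. Bone and several psychological outcomes have change tested or estimated. For continuous scales that are not formally tested, the baseline mean is also shown for the participants with follow-up data, which guards against a changing sample. The bloods row has no such safeguard, and numbers do fall: 48-month outcomes are dropped because so few participants remain.

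**Working it through.** The SAP gives no sample size, abnormality rate, analyte count or range coverage for bloods, so there is no figure to reproduce. Step 1 needs no outside assumption. Steps 2 to 5 are illustrations under stated assumptions.

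**1. What two counts can tell us.** For one test, let n participants have both a baseline and a follow-up value, with a abnormal at baseline and b abnormal at follow-up. The number of new abnormalities can lie anywhere from max(0, b − a) to min(b, n − a). With n = 30 (assumed) and a = b = 5, the range is max(0, 0) = 0 to min(5, 25) = 5. The same two counts fit no new cases and five new cases with five resolved. If some participants counted at follow-up have no baseline value, even the lower limit fails. Reporting baseline under the general rule therefore helps but does not settle the question.

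**2. How much could be pre-existing.** Assume 5% of values flagged per test (a central 95% range), normally distributed values, no treatment effect, and within-person correlation r between baseline and follow-up. By simulation, the chance of normal at baseline and abnormal at one follow-up visit is 4.1% at r = 0.5 and 3.4% at r = 0.7, against 5.0% abnormal in all. The share already abnormal is about (5.0 − 4.1)/5.0 = 18% and, using the unrounded simulated values (5.02% and 3.38%), (5.02 − 3.38)/5.02 = 33%. For a test on which participants commonly start out of range, the share would be higher.

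**3. Background rate of the any-test figure.** If it counts participants with at least one abnormal result among k independent tests, the chance for an unaffected participant at one visit is 1 − (1 − p)^k.

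| k | p = 5% | p = 2.5% |
|---|---|---|
| 10 | 40% | 22% |
| 20 | 64% | 40% |
| 30 | 79% | 53% |

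With p = 5% and a between-test correlation of 0.4 (simulated), it is 32% for 10 tests and 48% for 20.

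**4. What normal/abnormal reporting misses.** Let one analyte shift upward by 0.5 SD. Its abnormal rate becomes P(Z > 1.46) + P(Z < −2.46) = 7.9%, up from 5%. With n = 30 the expected number abnormal goes from 30 × 0.05 = 1.5 to 30 × 0.079 = 2.4. The any-test proportion over 20 independent tests goes from 64% to 1 − 0.95^19 × (1 − 0.079) = 65%. A shift of that size would hardly show in either figure.

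**5. Which shift table.** A baseline-against-worst-on-treatment table pools three visits. Under independence and no effect, the chance of normal at baseline and abnormal at least once is 0.95 × (1 − 0.95³) = 0.95 × 0.1426 = 13.5% per test. By simulation it is 10.6% at r = 0.5 and about 8% at r = 0.7. At a single visit the corresponding figures are 0.95 × 0.05 = 4.75%, 4.1% and 3.4%. The visit-by-visit form is the better one. It does not remove chance flags: across 20 independent tests at one visit, 50% to 56% of unaffected participants would still show at least one new abnormality (r = 0.7 and 0.5).

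**The case against.** The strongest reply is that the row is a deliberate, modest choice. The cohort is small and uncontrolled, individual tests matter only for overall safety, and descriptive reporting against laboratory norms without testing is defensible. That stands, and nothing proposed here needs a significance test.

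Three stronger readings are tempting, and the SAP does not support them.

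- **That safety rests only on an any-test count.** The quoted sentence plans normality of each test as well. Its last clause may even mean the numbers abnormal on whichever test is affected, in which case the background is about 5% per test per visit under the assumption above.
- **That the no-change hypothesis is never examined.** The general rule includes baseline, and medical safety is listed among the domains assessed there, so group-level proportions before and after can be compared. What is missing is change within persons and change on the measured scale.
- **That the any-test count is mostly chance.** This depends on an analyte count, range coverage and correlations that the SAP does not give. Several cases in the table are below one half.

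Disclosure is a fair further objection: the SAP itself warns that publication could identify individuals, and shift tables add small cells. That is a cost to manage. It does not justify counts that cannot be interpreted as change.

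**Conclusion.** The point holds in a limited form. As written, the safety-bloods row cannot distinguish abnormalities already present at baseline from new ones, and its normal/abnormal summary does not match its stated hypothesis. Adding baseline counts under the general rule would not cure this, as step 1 shows without any outside assumption. The row and the general rule also need reconciling on whether baseline is reported for bloods.

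The sizes are illustrative. The 18% to 33% pre-existing share rests on 5% flagged per test, normal values and a within-person correlation of 0.5 to 0.7. The background rate of an any-test count could lie anywhere from about 22% to 79% for 10 to 30 independent tests, depending on range coverage. None of this shows that the planned report would be wrong in a particular direction. It would leave the reader unable to tell who changed. The change is worth making because the remedy is cheap and standard.

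**What to change.** In the safety-bloods row:

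1. State that baseline is reported for bloods, in line with Analysis methods.
2. For each test, cross-tabulate baseline normal/abnormal against status at 12, 24 and 36 months separately, in participants with both values. Show new, persisting and resolved abnormalities, with the number of pairs at each visit. Apply no significance test.
3. Do not use a worst-on-treatment category, which accumulates chance flags over visits.
4. Either add the mean within-person change with a 95% CI for the measured values, or reword the hypothesis so that it claims only what a normality summary can show. The cross-tabulation alone does not reveal movement within the range.
5. Keep the any-test count, if wanted, as a secondary figure. Say exactly what it counts, and give the number of analytes and the range coverage so that its background rate can be judged.

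The cost is a few sentences of SAP text and a longer table, from data that the Outcomes section indicates are held. Small cells need a disclosure check, which fits the data-protection consultation already planned.
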